### 8.4 Recording of any AE/SAEs

The study defines AEs and SAEs per the national guidelines which are also found in the Serious Adverse Events handbook created by RTI ENVISION and the Task Force for Global Health:

**“Adverse event from MDA (AE-F-MDA)** is a medical event that takes place in an MDA program, causes concern in the medical and wider community and is believed to be caused by the drug(s) used. It can be caused by either administration of the drug or by a coincidental event that by chance happened after drug administration. Most AEs-f-MDA (adverse events from MDA) are self-limiting and treatable using simple remedies and are not usually required to be reported to national or international regulatory authorities.

**Serious Adverse Event (SAE)** is a regulatory term describing any untoward medical occurrence with any of the following characteristics:

- Results in death;
- Requires in-patient hospitalization;
- Results in persistent or significant disability;
- Is life-threatening; or
- Results in a congenital anomaly/birth defect.”

All adverse events will be recorded and followed up by the nurses on the team. The reporting of adverse events will be systematic and comply with national AE/SAE reporting guidelines to avoid any bias related to the wording of the question(s).

While the difference between “adverse events” and “serious adverse events” have been described above, there is also a level of severity which the study will also monitor: “The term “severe” is often used to describe the intensity (severity) of a medical event, as in the grading “mild”, “moderate”, and “severe”; thus a severe action need not be serious.” Reported adverse events will be classified according to their intensity (none, mild, moderate, and severe).

- Mild: easily tolerated, does not interfere with daily activity,

- Moderate: uncomfortable enough to interfere with daily activity,
- Severe: precludes daily activity (Given that a “severe” adverse event includes inability to complete daily activities, it will be classified as a possible SAE for the purposes of this study.)

The evolution of older complaints will be classified as: exacerbated, ongoing, and improved or resolved/none.

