The causal relationship of serious adverse events observed with the triple therapy will be assessed as: *Unrelated, Unlikely, Likely*. The study will utilize information collected by the clinical nurses using the “Conduct an AE Investigation” steps detailed in the Serious Adverse Event Handbook. It is important to note that the study will not follow-up “minor” or “moderate” adverse events up with the full investigative checklist prescribed by the handbook but will reserve this for “severe” adverse events and SAEs. The PI, supervisors, and independent monitors will meet to review these determinations. If the supervisory group questions the results of the clinical nurses’s investigations, it will perform its own investigation of the report as an addendum to the original report. Incidences will be analysed based on preferred terms and body system levels. “Severe” adverse events and SAEs occurring during exposures will be analysed based on 3 levels of selection per pre-existence and causality:

- Treatment emergent signs and symptoms (TESS), i.e., all AE during exposure to treatment or that were not pre-existing
- TESS without causality ‘unlikely’
- TESS with causality ‘likely’

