## 10 Timetable for Study Completion

[figure not shown]

The Primary outcome is

- The safety as can be measured by incidence of AEs/SAEs over one month following the co-administered MDA in comparison to a control group receiving the standard MDA regimen.

Secondary Outcomes are:

- Understanding the perceptions of the beneficiaries receiving the co-administration of azithromycin, ivermectin, and albendazole especially surrounding pill burden and the change in MDA distribution schedule.
- Understanding the perceptions of the co-administration strategy by the local health workforce as a means of PC-NTD drug delivery.
- A cost analysis comparing existing MDA unit costs from woredas within the region already on a standard MDA schedule with that of the co-administered woredas.

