## Appendix 4: AES Surveillance form

- 3.1. Community ID: |\_\_|\_|\_|\_|\_|\_|\_|\_|\_|\_|\_|
- 3.2. Participant ID |\_\_|\_|\_|\_|\_|\_|\_|\_|\_|\_|\_|
- 3.2.1. Dates of first filling-in for surveillance purposes |\_\_DD|\_\_MM|\_\_YY|
- 3.2.1.1. Which day(s), please underline D1, D2, D3, D4, D5, D6, D7, D8, D9, D10, D11, D12, D13, D14, D15, D16, D17, D18, D19, D20, D21, D22, D23, D25, D26, D27, D28, D29, D20
- 3.2.2. Place of first filling-in? 1. Survey site 2. Home 3. Other 99. unknown
- 3.2.3. If other in 4.1.2., specify the place.....
- 3.2.4. Did you take all the three drugs? 1. Yes 2. No 99. unknown
- 3.2.5. Did you regurgitate the drugs? 1. Yes 2. No 99. Unknown
- 3.2.6. When did you take the drugs? |\_\_DD|\_\_MM|\_\_YY|
- 3.2.7. How did you feel after taking the drugs? 1. Fine (better than before) 2. Same as before 3. Bad 98. Do not know
- 3.2.7.1. If the respondent says **fine (better than before)** for 4.1.8, review questions under 2.1 “**For complaints or events prior to the treatment**” to describe their evolution. Use the coding; 0 = **None**: the complaint has gone, 1=**Improved**: the complaint is significantly less than before the treatment, 2 = **Ongoing**: the complaint is the same as before the treatment, 3 = **Exacerbated**: the complaint increased after the treatment; to grade them as in the list below

| Events existing before the treatment |                     | complaints (tick as necessary) | Grade |
|--------------------------------------|---------------------|--------------------------------|-------|
| 4.1.8.1.1                            | Fever               |                                |       |
| 4.1.8.1.2                            | Itching/ground itch |                                |       |
| 4.1.8.1.3                            | Headaches           |                                |       |
| 4.1.8.1.4                            | Dizziness           |                                |       |
| 4.1.8.1.5                            | Tiredness           |                                |       |
| 4.1.8.1.6                            | Deafness            |                                |       |
| 4.1.8.1.7                            | Jaundice            |                                |       |
| 4.1.8.1.8                            | Weakness            |                                |       |
| 4.1.8.1.9                            | Fatigue             |                                |       |

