| 4.1.8.1.10                           | Nausea              |                                |       |
| 4.1.8.1.11                           | Vomiting            |                                |       |
| 4.1.8.1.12                           | Diarrhoea           |                                |       |
| 4.1.8.1.13                           | Abdominal pain      |                                |       |

- 4.1.8.1.14 Flatulence/dyspepsia
- 4.1.8.1.15 Constipation
- 4.1.8.1.16 Joint/muscular pain
- 4.1.8.1.17 Swelling of (upper/lower) limbs
- 4.1.8.1.18 Swelling of eyelids/abnormal feeling in the eyes
- 4.1.8.1.19 Rash/plaque
- 4.1.8.1.20 Scrotal reaction
- 4.1.8.1.21 Skin nodules
- 4.1.8.1.22 Worm expulsion
- 4.1.8.1.23 Haematuria
- 4.1.8.1.24 Lymphoedema
- 4.1.8.1.25 Elephantiasis
- 4.1.8.1.26 Hydrocele
- 4.1.8.1.27 Palpitation/tachycardia
- 4.1.8.1.28 Orthostatic hypotension
- 4.1.8.1.29 Others
- 4.1.8.1.30 **If other specify**.....
- .....
- .....

3.2.7.2. Did the respondent experience complaints after taking the 3 drugs? 1. Yes 2. No  
99. unknown

3.2.7.3. If yes, which one(s)? (See questions under 4.1.8.1).....  
.....  
.....

**3.2.7.4.** How would you qualify your main complaint (see questions under 4.1.8.2), after taking the 3 drugs **1 = Improved 2 = Ongoing 3 = Exacerbated 4= Resolved**

3.2.7.5. If the respondent says **Bad (worsened than before treatment) for 4.1.8**, review questions under 2.1 “**For complaints or events to prior to the treatment**” to describe **their evolution**. Use the coding; 0 = **did not feel sick**, 1=**mild**, 2 = **Moderate**, 3 = **Major/severe**; to grade them as in the list below

3.2.7.6.

| Adverse event due to worsened existing symptoms before treatment |                                    |            |      |
|------------------------------------------------------------------|------------------------------------|------------|------|
| Symptoms/signs                                                   | when did the side effects appeared | Evaluation | Code |

|            |                                                  | D1 | D2 | D3 | D4 | D5 | D8 | D2 | D8 |
|------------|--------------------------------------------------|----|----|----|----|----|----|----|----|
| 4.1.8.5.1  | Fever                                            |    |    |    |    |    |    |    |    |
| 4.1.8.5.2  | Itching/ground itch                              |    |    |    |    |    |    |    |    |

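### Section 8.4 defines the AE behind the primary outcome by community concern and believed drug causation, which the recording form does not test, and the form treats worsened earlier complaints inconsistently

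*Protocol*

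**What the plan says.** Section 10 states the primary outcome as "The safety as can be measured by incidence of AEs/SAEs over one month following the co-administered MDA", compared with a control group on the standard regimen.

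Section 8.4 fixes what an AE is: "The study defines AEs and SAEs per the national guidelines". The definition it then cites is an event that "causes concern in the medical and wider community and is believed to be caused by the drug(s) used". The following sentence adds: "It can be caused by either administration of the drug or by a coincidental event that by chance happened after drug administration". The same section

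- defines an SAE as any untoward occurrence with a listed serious consequence, with no causality condition;
- grades AEs from mild (easily tolerated) to severe;
- says "All adverse events will be recorded and followed up by the nurses on the team".

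Section 8.5 introduces treatment-emergent signs and symptoms (TESS) for severe AEs and SAEs. The widest level is "all AE during exposure to treatment or that were not pre-existing", and two narrower levels then filter by causality.

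Appendix 4 is the AE recording form. Item 3.2.7 asks: "How did you feel after taking the drugs? 1. Fine (better than before) 2. Same as before 3. Bad". Under *Fine*, earlier complaints are reviewed one by one in a table of pre-treatment events, where *Exacerbated* is a permitted code. Under *Bad*, they go to a table headed "Adverse event due to worsened existing symptoms before treatment". No such review is specified for *Same as before*. Section 3.3 of the form is a full symptom grid with onset day and severity grade, and it has no field for cause or concern.

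**The concern.** A definition built on concern and believed causation suits spontaneous programme reporting, where the aim is to find events worth investigating. As a trial endpoint it makes membership of the numerator depend on opinion. The control arm receives a familiar schedule and the trial arm receives up to nine tablets at once, each arm has its own four teams (section 8.6), and no masking is described. If belief decides what counts, the measured difference may partly reflect expectation.

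The protocol also gives two incompatible answers to what is counted. Under 8.4, an easily tolerated headache that worries nobody is not an AE. Under Appendix 4, it is ticked and graded as one. Two analysts could build different numerators from the same trial, each citing the protocol.

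The second difficulty is narrower. Whether a worsened earlier complaint lands under an AE heading depends on how the respondent answered one global question, and the form does not say whether *Exacerbated* in the *Fine* table counts.

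**Working it through.** **Passages side by side**

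| Place | Concern required? | Believed cause required? |
|---|---|---|
| 8.4, AE definition | Yes | Yes |
| 8.4, SAE definition | No | No |
| 8.4, mild grade | No; easily tolerated events are graded | No |
| 8.5, TESS level 1 (severe AEs and SAEs only) | No | No; causality enters at levels 2 and 3 |
| Appendix 4, section 3.3 | No field | No field |

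The sentence on coincidental events concerns the true cause. It allows the belief to be mistaken; it does not remove belief or concern as conditions.

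**The plan's own figure**

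Inputs from section 8.1: AE rate 7% in both arms, margin 1.5 points, power 90%, two-sided 95% interval, 190 people per gote, and gote rates of 6–8%. I read the last as mean ± 2 SD, so SD = 0.5 points and k = 0.005/0.07 = 0.071; this reading is an assumption. The cluster formula is

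c = 1 + (1.960 + 1.282)² × [2p(1−p)/m + 2k²p²] / δ²

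= 1 + 10.507 × [2(0.07)(0.93)/190 + 2(0.005)²] / 0.015² = 35.3, rounded up to 36.

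This matches the stated 36 gotes per arm, hence 36 × 190 = 6,840 people. The sample size is not in dispute.

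**What a filter does against an absolute margin**

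The 1.5-point margin equals 0.015 × 6,840 ≈ 103 people per arm. Take n = 6,840 and per-arm variance

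v(p) = [p(1−p) + 189 × 0.005² × (p/0.07)²] / 6,840,

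with SE = √(v_control + v_trial). Then P(non-inferiority) = Φ[(0.015 − observed difference)/SE − 1.96].

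Equal filter, true rates 7% and 8.5%:

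| Share counted in both arms (assumed) | Observed rates | Difference (points) | SE (points) | P(non-inferiority) |
|---|---|---|---|---|
| 100% | 7.00% / 8.50% | 1.500 | 0.475 | 2.5% |
| 75% | 5.25% / 6.375% | 1.125 | 0.412 | 15% |
| 50% | 3.50% / 4.25% | 0.750 | 0.336 | 61% |

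Unequal filter, which can act either way:

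- **Trial arm under-attributed.** True rates are 7% and 8.5%, with 90% counted in the trial arm only. Observed rates are 7.00% and 7.65%, a difference of 0.65 points, SE 0.462. P = Φ(0.85/0.462 − 1.96) ≈ 45% instead of 2.5%.
- **Control arm under-attributed.** There is no true difference (7% in both), with 90% counted in control only. Observed rates are 6.30% and 7.00%, a difference of 0.70 points, SE 0.440. P = Φ(0.80/0.440 − 1.96) ≈ 44%, against 91% with complete counting.

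The documents give no attribution or capture shares, so every share here is assumed.

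**Routing of a worsened earlier complaint in Appendix 4**

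| Answer to 3.2.7 | Complaint-by-complaint review | Heading |
|---|---|---|
| *Fine* | Yes, *Exacerbated* allowed | Pre-treatment events |
| *Same as before* | None specified | – |
| *Bad* | Yes | Adverse event |

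Items 3.2.7.2 to 3.2.7.4 (any complaint after the drugs, which ones, and how the main one evolved) and section 3.3 are not conditional on 3.2.7.

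**The case against.** The strongest reply is that the form, not the quoted definition, governs what is recorded. Nurses record all adverse events, section 8.4 calls reporting systematic, section 8.5 has participants rank events as mild or moderate, and section 3.3 of the form has no field through which belief could remove a non-serious symptom. The only causality field is in Appendix 5, for serious effects. That stands. A reader might infer that unblinded nurses' opinion decides what counts as an AE; the protocol does not say so. It names nobody whose belief is decisive, and the nurses' role as recorders does not establish a filter. If staff follow the form, the attribution effect is small.

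A reader might also infer that the same worsened headache is necessarily an AE in one person and not in another. The unconditional items and section 3.3 can still catch it in someone who answered *Fine* or *Same as before*. What remains is that the form does not say worsened earlier complaints belong there.

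TESS covers only severe AEs and SAEs, so its loose *or*, which read literally admits unchanged earlier complaints, is a wording slip and not a rival definition of the primary outcome. Finally, the direction of arm-dependent bias is unsettled: suspicion of a new regimen could raise counted events in the trial arm and work against non-inferiority.

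None of this repairs 8.4. If the form governs, the stated definition of the primary event is wrong as written.

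**Conclusion.** The AE definition in section 8.4 is unsuitable for the primary outcome and conflicts with the form, the mild grade and the SAE definition. This is stated content, not detail left to an analysis plan. Its effect depends on which text is followed: little if the form is, potentially decisive if 8.4 is applied literally. On the assumed shares, an equal filter raises false non-inferiority at the margin from 2.5% to about 15% (75% counted) or 61% (50% counted). An unequal filter of 10% can move the result substantially in either direction. These figures show sensitivity and do not forecast bias; they rest on the assumed shares, the planned 7% rate and the reading of 6–8% as ± 2 SD.

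The inconsistent routing of worsened earlier complaints is a separate and smaller defect. How many events it would misplace cannot be estimated from the protocol.

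**What to change.** - **Sections 8.4 and 10:** define the primary AE as any sign or symptom on the Appendix 4 list that is new, or worse than the pre-treatment record in Appendix 2, regardless of believed cause or community concern. Keep the national definition for programme reporting, and believed causality as a secondary breakdown.
- **Appendix 4:** ask every respondent about the evolution of every earlier complaint ticked in Appendix 2, and count *Exacerbated* as an AE whatever the answer to 3.2.7.
- **Section 8.5 (minor):** use the same new-or-worsened wording for TESS in place of *or*.

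The cost is a few sentences and small changes to the form, best made before its conversion to electronic capture; Appendix 2 already collects the baseline. The real downside is precision. Counted rates may rise in both arms while the 1.5-point margin stays fixed. As an upper illustration, at the 15.8% cited for the standard arm of the Mali study, p(1−p) is 0.158 × 0.842 = 0.133 against 0.07 × 0.93 = 0.065, which roughly doubles the binomial part of the variance. The assumed 7% should therefore be checked against the new definition.

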### 8.5 Analysis Plan of Reported AEs/SAEs

The study lead will conduct real time analysis of the data including rates and confidence intervals using the ODK system. (See **Section 8.9**) Adverse events will be coded per the WHO Adverse Reaction Terminology (WHO-ART) and Medical Dictionary for Regulatory Activities (MedDRA). They also be defined according to level of severity (mild, moderate, severe) as defined in Section 8.4. The study will create an independent Data Safety Monitoring Board (DSMB) composed of members of the FMOH as well as national and international medical experts. (See **Appendix 12: Charter of Data and Safety Monitoring Board**) As a safety measure, the study lead will convene an immediate teleconference with the medical doctor participating in the study and the DSMB given the following criteria:

- IF the rate of adverse events ranked as mild/moderate by participants differs significantly in the trial group as compared to the control group during the first two “Follow-up Days” (**Day 2, Day 4**) as well during subsequent review of the data at **Day 15**, and at the conclusion of the study on **Day 31** (to determine if the remainder of the worda can safely be treated via triple drug therapy).
- IF an SAE occurs, the study lead and the medical doctor will conduct an immediate analysis and convene a call with the DSMB members. The DSMB members will advise the medical doctor in making an initial decision about attribution and whether a formal DSMB meeting is required. (Note: Given that a “severe” adverse event includes inability to complete daily activities, it will be classified as a possible SAE for the purposes of this study.)
- At conclusion of the study on Day 31 (to determine if the remainder of the worda can safely be treated via triple drug therapy).

The causal relationship of serious adverse events observed with the triple therapy will be assessed as: *Unrelated, Unlikely, Likely*. The study will utilize information collected by the clinical nurses using the “Conduct an AE Investigation” steps detailed in the Serious Adverse Event Handbook. It is important to note that the study will not follow-up “minor” or “moderate” adverse events up with the full investigative checklist prescribed by the handbook but will reserve this for “severe” adverse events and SAEs. The PI, supervisors, and independent monitors will meet to review these determinations. If the supervisory group questions the results of the clinical nurses’s investigations, it will perform its own investigation of the report as an addendum to the original report. Incidences will be analysed based on preferred terms and body system levels. “Severe” adverse events and SAEs occurring during exposures will be analysed based on 3 levels of selection per pre-existence and causality:

- Treatment emergent signs and symptoms (TESS), i.e., all AE during exposure to treatment or that were not pre-existing
- TESS without causality ‘unlikely’
- TESS with causality ‘likely’

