| Title              | Safety of the co-administration of azithromycin, albendazole and ivermectin versus standard treatment regimens during mass drug administration (MDA) in Ethiopia: a cluster-randomized trial                                                                                                                                                                                                                                                                                                                                                                                                                                                                                                                                                                                                                 |
| Objective          | To establish the safety profile, assess the community acceptance, and weigh the economic advantages of a three-agent MDA combining azithromycin, albendazole (Alb), and ivermectin (Ivm) in comparison to the standard MDA regimen which separates the administration of azithromycin from the dually administered ivermectin and albendazole by a period of two weeks.                                                                                                                                                                                                                                                                                                                                                                                                                                      |
| Design             | A cluster-randomized non-inferiority trial to assess the safety, local acceptance, and economic advantages of combined MDA with azithromycin, albendazole, and ivermectin in one district in Oromia, Ethiopia. Within this district, a study group of 8,000 people will receive the triple drug co-administration. A control group of 8,000 people within the same district will receive the standard MDA treatment beginning with Ivm/Alb followed two weeks later with azithromycin. The study will randomly sort sub-district communities ( Gotes ) into the trial arm and the control arm. The study will compare the “baseline” of adverse events (AEs) and severe adverse events (SAEs) between the two arms to determine if the triple drug therapy is not inferior to the standard treatment. |

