## 8.8 Co-Administration Schedule

*The study will have two cohorts control arm, which will receive the usual MDA, and study arm which will receive the triple co-administration. Each arm will have approximately 6,800 people, 42 Gotes. Primarily, the clustering will be made by geography where 42 adjacent Gotes will be in one and the other 42, in another. Which cluster will be the control or study arm will be decided by simple lottery method.*

*After decision on the study arms, the study team will conduct the training and the actual co-administration for a 17-day period (three days for training and 14 days for actual co-administration and surveillance). In total, the entire study will take 45 days to complete.*

**On Day 1**, after the three-day co-administration training module described above, 60 households (HH) or roughly 300 people will be targeted for MDA subjects included in the study will receive concomitantly azithromycin (up to 1 g or four 250 mg tablets), ivermectin (up to 12 mg or four 3 mg tablets) and albendazole (one 400 mg tablet per included subject irrespective of height and age). This will mean that the four teams in the trial arm and the four teams in the control arm will have treated 1200 people each (300 x 4) by the end of Day 1. Teams will remain at the location of the MDA for the entire day and night on standby in case there are any immediate complaints from the targeted beneficiaries. Note that, as described in the “Intensified medical access precautions” section, a medical doctor will remain centrally located between within the woreda throughout the 14 actual days of distribution in the unlikely occurrence of a reaction to the medication.

**On Day 2**, the clinical nurses on each team, led by the three HDA members, will travel to all 60 households within their team’s catchment area to confirm that all 300 persons that received drugs on Day 1 are all healthy and to document any AEs/SAEs that may have occurred. This will also serve as opportunity for a person-to-person coverage survey for later analysis. At the end of the day, the four teams from each arm, together with the independent monitors, PI, supervisors, etc. will meet and discuss if there were any results that should cause concern. While the clinical nurses conduct the house-to-house visits, the HEWs on each team will move to the next group of 60 households targeted for the Day 3 MDA and mobilize that community.

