**On Day 17, 18**, the clinical nurses and HEW from each of the original four teams will perform one last house to house follow up of all the households that received the triple drug administration. (400 HH x 4 teams = 1600 HH) This will be the last active follow-up step.

**Day 19-30**, the HEWs will maintain the reporting form for another two weeks in the event of any additional complaints from the targeted beneficiaries. This will be completely passive and the HEW will only log complaints if they are reported by a beneficiary. On Day 30, all of the co-administration registers and forms will be collected for data analysis from the HEWs.

Note that in the “standard MDA” control arm, the process described above will be conducted twice. First, IVM/ALB MDA will take place for with 14 days of active surveillance then the Trachoma MDA will take place for 14 days of active surveillance. Passive surveillance will continue in the control arm for two weeks after that.

Once the 45th day of the study is reached in Oromia, the field implementation portion of the study will be complete. The DSMB will review the final data before making a recommendation on how the remainder of the population in the woreda should be treated. Should the DSMB and the FMOH agree, the remaining 4-5000 beneficiaries within Homesha will be targeted for co-administration. However, at this juncture, the RCT will be over. The study will move to strictly observational with the same enhanced supervision in place.

Table 3: Follow up Schedule for both the Trial and the Control Arms of the Study

|                                                    | Day 1 | Day 2 | Day 3 | Day 4 | Day 5 | Day 6 | Day 7 | Day 8 | Day 9 | Day 10 | Day 11 | Day 12 | Day 13 | Day 14 | Day 15 | Day 16 | Day 17 | Day 18 | Day 19-30 | Day 31 |
|----------------------------------------------------|-------|-------|-------|-------|-------|-------|-------|-------|-------|--------|--------|--------|--------|--------|--------|--------|--------|--------|-----------|--------|
| Actual Distribution                                |       |       |       |       |       |       |       |       |       |        |        |        |        |        |        |        |        |        |           |        |

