### ***DSMB Meetings***

Precluding an occurrence of adverse events at previously described percentage or an SAE, the DSMB will meet via phone conference at the start of the project, and at Day 31 of the trial. Additional DSMB teleconferences will be scheduled as the Chair recommends. The agenda will be prepared by the DSMB Chair in consultation with the study investigators.

At least five business days before the DSMB the Principal Investigator will send study materials to the DSMB members to allow time to review the material before the meeting. The Principal Investigator and team will be responsible for the preparation of meeting materials and all DSMB meeting arrangements.

Closed sessions of the DSMB will be attended only by the voting DSMC members, the Executive committee, and the study statisticians. The closed session may be called when the DSMC reviews the safety and impact data unmasked as to random assignment. At the discretion of the DSMC Chair, the committee can meet in Executive session with only the five voting members present to discuss issues and take formal votes as needed.

Meeting minutes will be prepared by the Chief Investigator for the trial. Draft minutes will be combined and distributed to the Chair for review and changes before distribution to the entire committee and study team members. The minutes shall summarize all recommendations.

DSMB members must make every effort to attend DSMB meetings. If a member fails to make a meeting, it should be ensured that the member makes the next meeting. If a member fails to make the second meeting, the member will be replaced.

All data presented to the DSMB is considered confidential, and cannot be revealed to those outside the study until after publication.

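### The DSMB comparisons at Days 2, 4 and 15 set the triple regimen against IVM/ALB only, and the concluding review is placed at Day 31 in 8.5 and the charter but at Day 45 in 8.8

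*Protocol*

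**What the plan says.** **Regimens.** The Study Protocol Summary gives the control arm "standard MDA treatment beginning with Ivm/Alb followed two weeks later with azithromycin". In section 8.8, on the trial arm's distribution day, "subjects included in the study will receive concomitantly azithromycin" along with ivermectin and albendazole.

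**Control calendar.** Section 8.8 says the process is run twice for controls: "First, IVM/ALB MDA will take place for with 14 days of active surveillance then the Trachoma MDA will take place for 14 days". Two weeks of passive surveillance follow. The section puts the whole study at 45 days.

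**Early trigger.** Section 8.5, repeated in the charter's terms of reference, has the study lead convene the DSMB if the mild/moderate event rate "differs significantly in the trial group as compared to the control group during the first two" follow-up days, named as Days 2 and 4. The same criterion applies at Days 15 and 31.

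**Concluding review, first version.** Section 8.5 lists a DSMB call "At conclusion of the study on Day 31 (to determine if the remainder of the worda can safely be treated via triple drug therapy". The charter repeats this, and its section on meetings says that, absent earlier triggers, "the DSMB will meet via phone conference at the start of the project, and at Day 31 of the trial".

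**Concluding review, second version.** Section 8.8 ends field work on the 45th day and continues: "The DSMB will review the final data before making a recommendation on how the remainder of the population in the woreda should be treated".

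**The concern.** The trial asks whether three drugs given together cause more adverse events than the same three drugs given in two rounds. A between-arm comparison answers that only once controls have had both rounds and been followed after each. At Days 2, 4 and 15 they have been followed after the first round only. The missing drug matters on the protocol's own reasoning. Section 8.1 builds its 7% planning rate on azithromycin, and it attributes IVM/ALB events largely to microfilarial death, which it expects to matter less in a community treated for several years.

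Neither 8.5 nor the charter says that the early tables compare a complete regimen with part of one. A DSMB shown a significant difference could take it for an effect of co-administration. The charter also makes the board responsible for deciding whether to recommend terminating treatment at the interim analysis.

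The second issue is that one protocol gives two dates for the same review. On the earlier date the arms have unequal follow-up after their last drug, and control surveillance is still open.

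**Working it through.** **1. Reproduce the 45 days (section 8.8).** 3 training + 14 IVM/ALB + 14 azithromycin + 14 passive = 45. The figure also equals 14 + 31, a second control cycle run to its own Day 31. The text does not say whether the 45 days include training. Counted from the first MDA day, control passive surveillance ends on Day 14 + 14 + 14 = 42.

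**2. Dosing days, counted from the first MDA day.** The triple arm is treated on Days 1, 3, 5, 7, 9, 11 and 13. Adding 14 gives control azithromycin on Days 15, 17, 19, 21, 23, 25 and 27. This is inferred from the order and length of the two rounds, as the protocol does not list the days. The first next-day visit after azithromycin is then Day 16 and the last is Day 28. At Days 2, 4 and 15 no control participant has been visited after azithromycin.

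**3. Days since last dose at each candidate review.**

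| Review day (MDA clock) | Triple arm, since dosing | Control arm, since azithromycin |
|---|---|---|
| 31 | 18 to 30 | 4 to 16 |
| 42 | 29 to 41 | 15 to 27 |
| 45 | 32 to 44 | 18 to 30 |

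At Day 45 controls have reached the 18-30 days that the triple arm had at Day 31. If the 45 days include training, the figure is 15-27, still the end of scheduled control follow-up. At Day 31 controls fall well short of the one-month window of the primary outcome (section 10).

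**4. How often the early criterion could be met with no true excess.** The inputs are:
- 7% for both complete regimens, using the planning rate in 8.1.
- r, the IVM/ALB-only rate. It is not in the protocol, so it is an assumption, taken from 3% to 6%.
- n per arm from 1,200 per distribution day (8.8): 1,200 at Day 2, 2,400 at Day 4, and 7 × 1,200 = 8,400 at Day 15.
- The 6-8% between-cluster range and 190 per gote (Table 2). Read as ±2 SD, SD = 0.005, so ICC = 0.005²/(0.07 × 0.93) = 0.000384 and the design effect is 1 + 189 × 0.000384 = 1.07. Read as ±1 SD, SD = 0.01, ICC = 0.001536 and the design effect is 1.29.

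The formula is the two-proportion z test, two-sided 5%: chance = Φ[(0.07 − r − 1.96·SE₀)/SE₁]. Here SE₀ uses the pooled rate, SE₁ the separate rates, and n is divided by the design effect. Example for Day 2, r = 5%, design effect 1.07: effective n = 1,119, SE₀ = 0.01004, SE₁ = 0.01003, chance = Φ(0.03) = 51%.

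Chance over design effects 1.29 to 1.0:

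| r | Day 2 | Day 4 | Day 15 |
|---|---|---|---|
| 3% | 98-99% | about 100% | about 100% |
| 4% | 81-90% | 98-99.5% | about 100% |
| 5% | 44-54% | 73-83% | about 100% |
| 6% | 14-17% | 23-29% | 64-75% |

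**The case against.** **The trigger only convenes a call.** This stands. It is not a stopping boundary, and a reader who infers that a significant early difference halts the trial goes beyond the text. Comparing acute tolerability with the first standard round is also a legitimate safety question, so the criterion need not go. What it needs is a correct description.

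**The probabilities rest on an undocumented rate.** This stands too. It is tempting to say that the early trigger fires when the regimens are equally safe. The protocol supports only that it can. The calculation also assumes that the full 7% shows as mild/moderate events at next-day visits. With only four gotes per arm by Day 2 (four teams in separate gotes, 8.3), a cluster-level t test with 6 degrees of freedom and a design effect of 1.11 (300 per gote) gives lower chances: 94%, 72%, 38% and 13% for r of 3, 4, 5 and 6%. The comparator mismatch itself needs no assumed rate.

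**A reader might infer that Day 31 undercounts control events.** That is likely but not shown. All control next-day visits are done by about Day 28, and controls have had such visits after both rounds. What is outstanding is the last house-to-house sweep and passive reporting. The documents establish unequal follow-up, not the size of any bias.

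**A reader might infer that Day 31 settles treatment of the rest of the woreda.** That is one side of the conflict. Section 8.8 requires final data, after Day 45, and the agreement of the ministry.

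**Day 31 might be a per-cycle clock.** Day 31 of the second control cycle is Day 45. But the charter says Day 31 of the trial, and 8.5 calls it the conclusion of the study. This reading would not cure Days 2 and 4 either.

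**Conclusion.** Wrong as written, on two counts.

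First, the between-arm criterion at Days 2, 4 and 15 compares the complete triple regimen with IVM/ALB only. This follows from the schedule alone. A significant difference can occur with no excess from co-administration. The chance runs from about 14% to 99% at Day 2, 23% to 100% at Day 4 and 64% to 100% at Day 15, under an assumed 7% for both complete regimens and 3-6% for IVM/ALB alone.

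Second, 8.5 and the charter place the concluding review at Day 31, while 8.8 places it at Day 45. At Day 31 controls have 4-16 days since azithromycin against 18-30 days since dosing in the triple arm, and control passive surveillance is open until at least Day 42. This rests on control azithromycin starting at about Day 15.

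The primary outcome in section 10 is still defined against the full standard regimen, so neither count changes its definition.

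**What to change.** - In 8.5 and the charter, keep the early safety calls and the SAE trigger. Label the Day 2, 4 and 15 tables as triple regimen v IVM/ALB only, and state that they do not compare the two complete regimens.
- Base the concluding between-regimen comparison on data gathered after the control arm's second-round follow-up is complete.
- Reconcile 8.5, 8.8, Table 3 and the charter (terms of reference and meetings) on the date of the concluding DSMB review, and say which clock the day numbers use and whether it includes the three training days. The column headings of Table 3 end at Day 31 although its title covers both arms. Its day markings are not legible in the text at hand, so check them against the agreed date.

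Cost: wording changes in the protocol and charter, and about two weeks' delay of one teleconference. No additional data are needed.
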